# Study protocol for single-center, open-label, randomized controlled trial to clarify the preventive efficacy of electrical stimulation for muscle atrophy after trauma

**DOI:** 10.1186/s13063-018-2872-4

**Published:** 2018-09-14

**Keywords:** Pelvic fracture, Electrical muscle stimulation, Rehabilitation

## Abstract

**Background:**

Management of trauma involves long-term bed rest even when muscle strength in the lower extremities is preserved. Prolonged bed rest reduces muscle mass and causes muscle atrophy. A recent study reported the efficacy of rehabilitation using electrical muscle stimulation (EMS) for muscle strength maintenance in intensive care unit patients with disturbance of consciousness. However, despite the expected benefits of EMS in maintaining muscle strength, little is known about its efficacy in trauma patients.

**Methods/design:**

A single-center, open-label, randomized controlled trial of 40 patients with pelvic fracture to test the effectiveness of 14 days of EMS. The primary outcome will be change in cross-sectional area of the thigh muscle between pre and post intervention, as measured on computed tomography images. We will analyze the primary endpoint by analysis of covariance (ANCOVA) and analyze the secondary endpoints in an exploratory manner.

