### Sample size

Target sample size: 50 patients (25 each in the intervention group and control group).

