### Rationale

In a previous study of disuse muscle atrophy in patients with consciousness disturbance in the intensive care unit (ICU) [4], change in cross-sectional area was found to be 0.85 on average after 1 week of conventional rehabilitation (without EMS). The ratio of cross-sectional area pre and post intervention changed by 0.85 after 2 weeks of EMS-integrated rehabilitation (EMS group) compared with 0.72 after 2 weeks of conventional rehabilitation (control group), for a difference of 0.13 between the groups. For the present study, we recalculated the sample size for analysis of covariance (ANCOVA) with the standard deviation of 0.15 for both groups, alpha error of 0.05, power of 0.8, and covariance of 1. A sample size of 44 was required based on the calculation. Thus, we revised the manuscript to include 25 patients for each group.

To calculate sample size for the present study, we determined that approximately 25 pelvic fracture patients required 2-week hospitalization at the Department of Emergency Medicine and Critical Care, Center Hospital of the National Center for Global and Medicine between 2015 and 2016, with no dropouts including those due to death. Thus, a total of 50 patients (25 in each group) is required for the present study.

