## Trial status

Protocol version: 1.1

Study period: 14 November 2017 to 31 December 2019.

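### The abstract plans 40 patients but the sample size section plans 50; 40 misses the stated power, and the past admission count does not justify 50 and may not supply it

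*Protocol article*

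**What the plan says.** The protocol article gives the size of the trial in three places.

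- **Abstract, Methods/design:** "A single-center, open-label, randomized controlled trial of 40 patients with pelvic fracture to test the effectiveness of 14 days of EMS".
- **Sample size:** "Target sample size: 50 patients (25 each in the intervention group and control group".
- **Rationale:** the inputs are a ratio of post- to pre-intervention muscle area of 0.85 with stimulation against 0.72 without, "for a difference of 0.13 between the groups", an SD of 0.15 in both groups, and "alpha error of 0.05, power of 0.8, and covariance of 1". The result is stated as "A sample size of 44 was required based on the calculation", followed by "Thus, we revised the manuscript to include 25 patients for each group".

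A second paragraph of the Rationale, introduced as a sample size calculation, reports that "approximately 25 pelvic fracture patients required 2-week hospitalization" at the centre between 2015 and 2016, with no dropouts. It then concludes that 50 patients in total are required. The Study setting section names one hospital. Trial status gives "Study period: 14 November 2017 to 31 December 2019".

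**The concern.** Two planned sizes stand in the current text. The smaller one lies below the number that the protocol itself says is needed for power of 0.8. A reader who relies on the abstract would take the trial to be complete at a size that does not meet its own design requirement. In an open-label trial whose assessors and statisticians are unblinded, the enrolment target should have a single value.

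The second paragraph of the Rationale adds a separate problem. A count of past admissions describes how many patients might be available. It cannot show how many are required. Here the count of about 25 reappears as the size of each arm. Read as what it is, an availability figure, it raises doubt about whether 50 can be reached by the stated closing date. If it cannot, the power that the plan reports is not the power that the trial would have.

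**Working it through.** **Inputs.** From the Rationale: difference 0.85 − 0.72 = 0.13; SD 0.15; alpha 0.05; power 0.8; about 25 admissions in 2015–2016. From Sample size: equal allocation. From Trial status: 14 November 2017 to 31 December 2019. Assumptions of mine: two-sided alpha (sidedness is not stated), one covariate that explains no variance, a constant admission rate, and enrolment open for the whole study period.

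**Step 1: reproduce the 44.** The standardised difference is 0.13 / 0.15 = 0.867. The normal approximation gives 2 × (1.960 + 0.842)² × (0.15 / 0.13)² = 20.9, so 21 per arm, or 42. The two-sided t-test (noncentral t) gives 21.9, so 22 per arm, or 44. ANCOVA with one covariate and no variance reduction also gives 22 per arm, with power 0.801. A one-sided test needs only 17 to 18 per arm (34 to 36 in total), so the stated figure is two-sided. The protocol's 44 is correct.

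**Step 2: power at each size.** The noncentrality is 0.867 × √(N/4), with N − 3 degrees of freedom.

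| Total N | Where it appears | Noncentrality | Power |
|---|---|---|---|
| 40 | Abstract | 2.74 | 0.761 |
| 44 | Rationale, calculated requirement | 2.87 | 0.801 |
| 50 | Sample size and Rationale, target | 3.06 | 0.851 |

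**Step 3: accrual implied by the admission count.** The study period is 777 days, and 777 / 365.25 = 2.13 years.

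- *Count covers both calendar years:* 25 / 2 = 12.5 a year, and 12.5 × 2.13 = 26.6, about 27 admissions. With all 27 enrolled, power is about 0.58, and the difference detectable with power 0.8 is about 0.17 instead of 0.13.
- *Count covers one year:* 25 × 2.13 = 53.2, about 53 admissions. Reaching 50 needs 50 / 53.2 = 94% of them randomised. Reaching 44 needs 44 / 53.2 = 83%. At 80% uptake about 43 are enrolled (power 0.79), and at 60% about 32 (power 0.66).

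**Step 4: could the covariate make up the shortfall?** At 27 patients the residual SD would have to fall by the factor 0.13 / 0.169. The covariate would then have to explain 1 − (0.13 / 0.169)² ≈ 0.41 of the outcome variance. The protocol assumes nothing of the kind.

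**The case against.** The best defence is that the plan proper is clear. The section headed Sample size gives 50, the Rationale repeats 25 per arm, and it says that the size was recalculated and the manuscript revised. The abstract's 40 is then most naturally a figure that was not updated. That is a reasonable inference, and it makes the repair small. It does not remove the contradiction, because both figures stand in the published text.

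Several stronger readings are tempting, and the document does not support them.

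- *Three rival sizes.* A reader might count 44 as a third planned size. The Rationale presents it as the calculated requirement and then sets 50 above it, so the two agree.
- *The power claim is false.* At the stated target of 50, power is 0.85. It falls below 0.8 only if 40 is the true size or if fewer than 44 are enrolled.
- *The centre cannot supply 50.* The two-year reading of the count is the more natural one, but the wording does not exclude a single year, on which about 53 admissions are expected. The count is also not of the eligible population. It covers patients who needed two weeks in hospital, while the Inclusion criteria ask for bed rest of at least one week and particular fracture types. The eligible pool could be larger or smaller.
- *Stopping at 40 or 50 after looking at the data.* The article describes no interim look, so this would be speculation.
- *The six patients above 44 are a dropout allowance.* The article does not say so; it reports no dropouts.
- *The covariance input is an error.* It is loose wording. Read as one covariate that explains no variance, it returns exactly 44, and that assumption is conservative.

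**Conclusion.** The point holds in two parts of different weight.

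The conflict between 40 and 50 is certain and needs correction. At 40, power on the protocol's own inputs is about 0.76 against the stated 0.8; at 50 it is about 0.85. These values rest on a two-sided 5% test and a covariate that explains no variance. A prognostic baseline measure would raise all of them.

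The step from about 25 past admissions to 50 required patients does not follow, whatever period the count covers. What the count implies for accrual is conditional: about 27 admissions and power of about 0.58 at best on the two-year reading, or about 53 admissions with some 94% to be randomised on the one-year reading. Both assume that the past rate continues and that the count approximates the eligible pool. Neither reading sits comfortably with a target of 50 by the closing date, but the document does not show that 50 is out of reach.

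**What to change.** 1. Change 40 to 50 in the abstract.
2. In the Rationale, state 44 as the calculated minimum and 50 as the target. If a reason is given for the extra six patients, it must be the sponsor's own.
3. Delete the inference from about 25 past admissions to 50 required. Keep the count only as information on feasibility.
4. State which period the count covers and what share of admissions is expected to be eligible and to consent. Then reconcile expected accrual with the study period: either say that enrolment continues to 50 whatever the calendar date, or give the power at the number expected by 31 December 2019.
5. Optional: reword the covariance input as one covariate, with no variance reduction assumed.

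Items 1 to 3 and 5 cost wording only. Item 4 may cost a later closing date or a less favourable power statement.

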**Conclusion:**

If our hypothesis is confirmed, this study will provide evidence that the use of EMS can be effective in preventing muscle atrophy.

**Trial registration:**

UMIN registration number: UMIN000030190. Registered on 1 December 2017.

**Electronic supplementary material:**

The online version of this article (10.1186/s13063-018-2872-4) contains supplementary material, which is available to authorized users.

## Background

Management of trauma, such as cervical spinal cord injury and pelvic fracture, involves long-term bed rest even when muscle strength in the lower extremities is preserved. Prolonged bed rest reportedly reduces muscle mass by 6–40% [1]. After just a few months or years of muscle strength impairment and muscle atrophy, muscle strength may not be completely regained. This contributes strongly to a decline in activities of daily living (ADL) [2]. Physiotherapy including resistance exercises and joint exercises can be started while patients are on bed rest. However, these exercises are not sufficient by themselves to maintain muscle strength; load-bearing exercises are required to maintain muscle strength [3].

A recent study reported the efficacy of rehabilitation using electrical muscle stimulation (EMS) for muscle strength maintenance in intensive care unit patients with disturbance of consciousness [4], clinical illness [5], and spinal cord syndromes [6]. However, despite the expected benefits of EMS in maintaining muscle strength, little is known about its efficacy in trauma patients without lower limb injury who are placed on bed rest immediately after trauma even when muscle strength is unaffected.

In this study, we investigate whether EMS plus conventional physiotherapy is more effective than conventional physiotherapy alone for maintaining muscle strength or retarding its impairment in patients with pelvic fracture who are placed on bed rest.

## Methods/design

### Study setting

This trial is conducted at the Center Hospital of National Center for Global Health and Medicine.

### Objective

To investigate whether addition of EMS to conventional rehabilitation retards loss of muscle mass in trauma patients who require bed rest for at least 1 week despite no initial impairment in muscle strength in the lower extremities.

### Trial design

Single-center, open-label, randomized controlled trial.

### Eligibility criteria

#### Inclusion

Age 20–90 years, able to provide informed consent themselves or via a legal representativeTrauma inpatient with either unstable pelvic fracture or pelvic fracture at the site where load will be applied. Patients with pelvic fracture included those with an AO classification of 61B2.3 (open book), 61B3.1, 61B3.2, 61C2.1, 61C2.2, and 61C2.3, as well as those who were recommended to rest in bed in supine position for at least 1 week as determined by orthopedic surgeons that we consulted.Requires bed rest for at least 1 weekComputed tomography (CT) scans of pelvis and lower extremities taken at the time of hospital admission

#### Exclusion

Pacemaker (contraindicated for use with EMS devices)History of neuromuscular disorder (poliomyelitis, myasthenia gravis, or Guillain-Barré syndrome) and/or cerebral infarction (paralysis or contracture)Disturbance of consciousness impairing ability to follow instructionsBed-bound or wheelchair-bound, or with femoral neck fracture and/or intertrochanteric femoral fractureScore of 2 or more for intestinal or pancreatic trauma (based on the Abbreviated Injury Scale (AIS) [7])Fracture or skin injury (except for contusion) at the site for EMS application (thigh, knee joint, or ankle joint)Inability to provide informed consentParticipation judged to be inappropriate by the physician in charge

Rationale for criteria 1–2: use of EMS may aggravate preexisting conditions or evaluation may not be conducted accurately.

### Interventions

#### Intervention group

For electrical muscle stimulation, we will use the AUTO Tens PRO Rehabili Unit B-SES (belt electrode skeletal muscle electrical stimulation; Medical Device Certification No.: 224AHBZX00015000) and G-TES (general therapeutic electrical stimulator; Medical Device Certification No.: 228AGBZX00036000) devices (both Homer Ion Co. Ltd., Tokyo, Japan). We will wrap the AUTO Tens PRO belt electrodes around the abdomen, proximal aspect of the legs, and ankles for electrical stimulation of the entire lower extremities. Patients will receive one 20-min EMS session daily, consisting of 5-s stimulations (20 Hz) separated by 2-s rest intervals, for 5 days per week for 2 weeks. The output current will be in the range 2–15 mA, and the current will be increased to the maximum tolerable level within 3 days of starting rehabilitation. A co-investigator who is a physical medicine and rehabilitation physician will supervise the 14-day EMS protocol. In parallel, we will provide conventional physiotherapy on the same day as the EMS session (also for 20 min daily). Conventional physiotherapy will consist of (1) hip and ankle joint mobility exercises and (2) lower limb-strengthening exercises in a supine position.

#### Control group

Patients will receive the conventional physiotherapy protocol alone.

### Criteria for discontinuation

Failure to elicit palpable muscle contraction at maximum tolerable current after three daily sessions due to patient discomfortAny injury to the skin and/or striated muscleVoluntary withdrawal of consent from the trial

Rationale for criteria 1 and 2: to eliminate the influence of these factors on the evaluation of efficacy and safety.

Rationale for criterion 3: to respect participants’ voluntary decision.

### Outcomes

#### Primary endpoint

Change in cross-sectional area of thigh muscle between pre and post intervention, as measured on CT images

#### Secondary endpoints

We will measure all secondary endpoints on the same dates that CT imaging is obtained.Change in cross-sectional area of calf muscle between pre and post intervention, as measured on CT imagesReduction in thigh and calf circumference, measured at the same sites as CT image measurementsThigh and calf circumference measured on CT imagesChanges in manual muscle testing results

We will obtain baseline CT data of the region including the pelvis and lower extremities at the time of admission (pre intervention, from day − 4 to day 0) and measure cross-sectional area of the thigh and calf muscles. Day 1 is defined as the first day of rehabilitation intervention.

To evaluate the outcomes of intervention, we will obtain post-intervention plain CT data of the region including the pelvis and lower extremities and measure cross-sectional area of the thigh and calf muscles on day 14 of intervention (or before the end of day 17). Specifically, we will obtain the following measurements.Thigh: height at the center of a line linking the greater trochanter and knee joint cleftCalf: height at the center of a line linking the fibular head and external condyleThigh and calf muscle cross-sectional area: we will extract areas with intensity in the range of 30 to 100 Hounsfield Units (HU) from CT slices and measure cross-sectional area to determine change between pre- and post-intervention values

We will obtain CT scans in the supine position with both legs in the neutral position, with a pillow placed under both legs to avoid compression of the posterior aspect of the legs from the CT bed. We will ask patients to relax to minimize the influence of morphological changes due to muscle contraction. The following CT machines will be used:Aquilion™ CX TSX-101A/NA, Application Ver. V4.62JR019 (Toshiba Medical Systems Corp., Tokyo, Japan)SOMATOM Definition Flash VA44A, Somaris/7 Syngo CT 2012BWinNT 6.1, Service Pack 1, VA44A_08_P16 (Siemens Healthcare, Forchheim, Germany)Aquilion ONE™ TSX-301A/2A, Application Ver. V4.7JR004 (Toshiba Medical Systems Corp.)Discovery CT 750HD, Application Software, 11 MW44.11.V40_PS_HD64_G_GTL (General Electric Healthcare, Waukesha, WI, USA)

### Sample size

Target sample size: 50 patients (25 each in the intervention group and control group).

### Rationale

In a previous study of disuse muscle atrophy in patients with consciousness disturbance in the intensive care unit (ICU) [4], change in cross-sectional area was found to be 0.85 on average after 1 week of conventional rehabilitation (without EMS). The ratio of cross-sectional area pre and post intervention changed by 0.85 after 2 weeks of EMS-integrated rehabilitation (EMS group) compared with 0.72 after 2 weeks of conventional rehabilitation (control group), for a difference of 0.13 between the groups. For the present study, we recalculated the sample size for analysis of covariance (ANCOVA) with the standard deviation of 0.15 for both groups, alpha error of 0.05, power of 0.8, and covariance of 1. A sample size of 44 was required based on the calculation. Thus, we revised the manuscript to include 25 patients for each group.

To calculate sample size for the present study, we determined that approximately 25 pelvic fracture patients required 2-week hospitalization at the Department of Emergency Medicine and Critical Care, Center Hospital of the National Center for Global and Medicine between 2015 and 2016, with no dropouts including those due to death. Thus, a total of 50 patients (25 in each group) is required for the present study.

## Methods

### Assignment of intervention

#### Enrollment procedure

Patients who are deemed eligible for the study according to the inclusion and exclusion criteria will be enrolled in the study within 1–2 days after hospital admission. Before entry, patients themselves must sign informed consent forms. In the case that patients can follow instructions, but dementia or mental retardation makes the voluntary nature of their actions unclear, their legal representatives (third-degree relatives and legal guardians) must provide written informed consent.

### Allocation

A computer-generated random number table will be prepared by an individual who is not an investigator. The table will be stored in a designated safe by the coordinator of the outpatient division of the Department of Emergency Medicine and Critical Care, who is not involved in the study. Study investigators who are the physician in charge of admitted patients satisfying the enrollment criteria will report the admissions to the coordinator. The coordinator will then allocate patients to either of the groups using the prepared random number table and will notify the investigators of the allocation results.

### Participant data collection

See Fig. 1 for details of the data collection schedule. Figure 2 shows the Standard Protocol Items: Recommendations for Interventional Trials (SPIRIT) schedule for the trial protocol.Participant background: age, sex, medical history, height, weight, diagnosis at time of admission (type of trauma, AIS score, ADL, Functional Independence Measure score [8], and Barthel ADL Index [9])Physical findings for the EMS group only: blood pressure, heart rate, oxygen saturation, and level of consciousness before starting EMS, 10 min after starting EMS, and on completion of EMS; pain level using a numerical rating scale [10] during EMS; thigh and calf circumference at the time of admission (pre intervention) and on days 14–17 (post intervention); manual muscle testingImaging diagnosis: measurements of cross-sectional thigh and calf area on plain CT images taken at the time of admission (from day −  4 to day 0) and at the end of rehabilitation (days 14–17)Clinical testing: creatinine kinase (CK) level on days 0, 3, 7, and 14–17Functional Independence Measure score and Barthel ADL Index at 1 and 2 months after the injury

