### Statistical analysis

For all participants who satisfy the inclusion criteria and start receiving the test intervention, as a definitive statistical analysis model, ANCOVA (regression model) was used to evaluate the effect of the treatment. The outcome measure was the rate of reduction, and independent variables included the treatment method, possible confounders in randomization, and baseline measure of muscle mass and analyze the secondary endpoints in an exploratory manner.

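### The endpoint list and the data collection list disagree on whether manual limb circumference and manual muscle testing are measured in control patients

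*Protocol article*

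**What the plan says.** The Secondary endpoints section of the protocol article lists four outcomes: calf muscle cross-sectional area on CT, thigh and calf circumference measured at the CT sites, circumference read from the CT images, and change in manual muscle testing. On timing it says "We will measure all secondary endpoints on the same dates that CT imaging is obtained". It names no arm.

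The Participant data collection section contains an item that opens "Physical findings for the EMS group only: blood pressure, heart rate, oxygen saturation, and level of consciousness before starting EMS". The same item goes on, separated by semicolons, to pain during stimulation, then to circumference at admission and on days 14–17, and ends with manual muscle testing. The next item, on imaging, starts only after that. The other items (background, imaging, creatine kinase, and the Functional Independence Measure and Barthel scores) carry no arm restriction.

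The Background asks whether EMS plus physiotherapy is "more effective than conventional physiotherapy alone for maintaining muscle strength or retarding its impairment". The Objective section is narrower and concerns loss of muscle mass. For the secondary endpoints, the Statistical analysis section plans only to "analyze the secondary endpoints in an exploratory manner".

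**The concern.** Vital signs, consciousness and pain around a stimulation session can exist only in the arm that is stimulated, so restricting those to EMS patients is sensible. Circumference and manual muscle testing are different in kind: they are listed as endpoints of a two-arm randomised comparison and need values from both arms.

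If site staff or the case report form followed the collection list literally, only a before/after change in the EMS arm could be reported for these two measures. The sample size rationale expects muscle loss in both arms over two weeks (pre/post area ratios of 0.85 with EMS and 0.72 without). Under that expectation, a change in the EMS arm alone cannot separate an effect of EMS from the course of bed rest with physiotherapy. Manual muscle testing matters most here, because no other listed endpoint measures strength.

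**Working it through.** **Step 1: set the two lists side by side.**

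| Secondary endpoint | Arm stated in Secondary endpoints | Where it appears in Participant data collection | Control data if the list is followed literally |
|---|---|---|---|
| Calf cross-sectional area, CT | none | imaging item, no arm restriction | yes |
| Thigh and calf circumference, by hand | none | EMS-only item | no |
| Thigh and calf circumference, CT | none | not named as such; readable from the CT images in the unrestricted imaging item | yes |
| Manual muscle testing | none | EMS-only item | no |

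Count: 2 of 4 fall under the restriction and 2 of 4 do not.

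**Step 2: size of the gap.** The Sample size section gives "Target sample size: 50 patients (25 each in the intervention group and control group"). On the literal reading, 0 of 25 controls would have either measure, so no between-arm contrast could be estimated for it.

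**Step 3: what could be recovered.** Girth can be read from CT images taken in both arms, and CT circumference is already an endpoint. Manual muscle testing that was not done at baseline and at days 14–17 leaves no record to go back to.

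**Step 4: does the literal reading fit the rest of the article?** Not comfortably. Circumference is due at admission. The Enrollment procedure section enrols patients 1–2 days after admission, and under the Allocation section the arm is known only once the coordinator has been told of an eligible patient. At admission there is no EMS group, so an admission measurement cannot be confined to it. This suggests that the restriction was meant for the session observations only.

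**Step 5: confirm that the primary analysis is untouched.** The Rationale section uses an effect "for a difference of 0.13 between the groups" and a "standard deviation of 0.15 for both groups, alpha error of 0.05, power of 0.8, and covariance of 1". I read the last term as one covariate and assume a two-sided test, since sidedness is not stated.
- Effect size: f = (0.13 / 0.15) / 2 = 0.433.
- F test with 1 and N − 3 degrees of freedom and noncentrality N × f².
- N = 44: power 0.801, which reproduces the plan's 44.
- N = 50: power 0.851.

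None of these inputs involves circumference or manual muscle testing.

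**The case against.** The strongest reply is that this is a wording slip and no one-arm design was intended. The Secondary endpoints section ties all four endpoints to the CT dates, and CT is taken in every patient. The admission timing in Step 4 points the same way. The collection section refers to Fig. 1 for the detailed schedule and to Fig. 2 for the SPIRIT schedule. Neither is shown in the text available here, and either might list these measures for both arms. The list was also flattened when the text was extracted, although the semicolons and the start of the imaging item favour the literal reading.

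This reply stands as far as intent goes. A reader might infer from the collection list that the trial has settled on measuring these endpoints in one arm. The documents do not support that inference, because another section says otherwise. The reply does not remove the defect. The text names an arm for measures that the endpoint list treats as trial-wide. Even if the figures do show both arms, they would then disagree with the text.

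A second reply concerns importance. These endpoints are exploratory, the formal Objective is muscle mass, and thigh area, calf area and CT girth remain comparable between arms. So do the two functional scores. This also stands. A reader might conclude that the trial could not meet its objective, but the documents do not support that: what is at risk is the randomised comparison of strength raised in the Background.

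**Conclusion.** The plan is wrong as written: the two sections contradict each other and must be reconciled. The point should be fixed, but it does not threaten the trial's main result.

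If the collection list governs, 2 of 4 secondary endpoints have no control data. For manual circumference the loss is partial, because CT girth stands in for it. For manual muscle testing it is complete and permanent, and with it goes the only between-arm comparison of strength. If the Secondary endpoints section governs, nothing is lost and only the text needs correcting.

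The conclusion rests on the article's text alone. The schedule figures and the case report form were not available, and either could show which reading is applied in practice. The primary endpoint, its ANCOVA and the sample size are unaffected under both readings.

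**What to change.** In Participant data collection, take thigh and calf circumference and manual muscle testing out of the EMS-only item. List them in an item for all randomised patients, at admission and on days 14–17, which matches the CT dates set in Secondary endpoints. Keep as EMS-only just the observations made around stimulation sessions: blood pressure, heart rate, oxygen saturation, consciousness and pain. Check that Figs. 1 and 2 and the case report form agree.

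State that both endpoints are compared between arms within the exploratory analysis already planned. This point does not require a particular model for manual muscle testing.

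The cost is a small change to the collection list and the form, plus a brief bedside measurement per control patient around CT dates already planned. No treatment or clinical rule changes.
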